  - d. For those individuals who refuse screening, are not eligible or opt not to participate, we will record only their temporary study code on the recruitment screen. We will submit this list of temporary study codes to Head Start personnel for two reasons: 1) to avoid inadvertent re-approaching; and 2) so that Head Start can supply the study team with an anonymized demographic description of this population with a de-identified list of demographic characteristics, (Attached in the study binder). Specific variables will include only those that Head Start keeps for programmatic reasons (the equivalent of existing clinical data): age, language spoken, place of birth, race, ethnicity, education, work status, marital status, household type (single or double-headed household), number of people in household, living situation, income, health insurance status, type of government assistance.
4. Written Informed Consent: After the two screens are administered and the potential subject is found to be eligible, the subject will be enrolled (if willing) into either the RCT or into a small supplemental pilot study of 'PSE Lite.' Immediately following the signing of the consent form, the following will happen:
- a. Subjects will be administered either the MacCAT-CR immediately after the consent form in order to ensure that subjects with limited cognitive capacities and/or major mental illness, including psychosis, are safeguarded from being in the study.
  - b. Subjects will be screened for suicidal ideation in order to safeguard subjects with high suicidal ideation. Our crisis protocols will be activated as necessary (Crisis Management Plan, Domestic Violence Protocol, Referral of Clients with Trauma or Substance Use – each protocol is provided in the study binder).
5. Once participants have completed the safeguards outlined in above, we will collect the following data from all mothers enrolled in the study *prior to* randomization. The interviews will be completed in private rooms at the Head Start center, or in subjects' homes (subjects' choice). The Baseline Survey will comprise the following valid and reliable scales:
- a. Children with Special Health Care Needs Screener

- b. Perceived Stress Scale
  - c. M.I.N.I. Depression Module (current or recurrent Major Depressive Episode (We will use the data from the second verbal screen for this. We have added this permission to the written consent form.))

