  - d. Quick Inventory of Depressive Symptoms. Beck Anxiety Inventory
  - e. Mental Health Service Use questions (adapted from Collaborative Psychiatric Epidemiology Surveys)
  - f. Medical Outcomes Study – Social Support Survey
  - g. Social functioning (Social Adjustment Scale-Self Report)
  - h. Problem Solving Questions (Social Problem Solving Inventory)
  - i. Substance Use (CAGE-AID and AUDIT)
  - j. Coping Questions (Brief COPE)
  - k. Rosenberg Self-Esteem Scale
  - l. Behavioral Activation for Depression Scale
  - m. Pearlin Mastery Scale
  - n. Stressful Life Events Questionnaire
  - o. Modified PTSD Symptom Scale
  - p. Demographics
  - q. Behavioral Activation Score
6. If randomized to the PSE group, we will employ a team of 4 to 6 research staff (at any given time) to serve as interventionists (referred to as educators or providers). The educators will deliver up to 6 PSE sessions with their clients, each session expected to take 30-45 minutes. Sessions will be delivered either weekly or biweekly, according to the wishes of the subject – with a full course of PSE expected to last 8 weeks. Sessions will be delivered at a location of the subject's choosing. In addition to PSE, intervention subjects will be periodically screened with the PHQ-9 as part of 3 out of the 6 PSE sessions. A score of 15 or greater will require the educator to refer the mother to more definitive mental health care. These referrals will be "activated," meaning that the PSE educators will employ motivational interviewing techniques to help the mothers follow through with the referrals. Lastly, educators will phone their clients monthly to conduct brief "booster session" check-in's.
- Request to audiotape a randomly selected PSE will be embedded in the initial consent form; this will be offered to all subjects for the sake of monitoring treatment fidelity. It will be made clear that subjects can refuse audiotaping but still partake in the rest of the study.
7. Control group: We have chosen our control group to best approximate "usual care" in Head Start. Thus, families will be followed by their Head Start caseworkers, and screened periodically for depression when deemed necessary by Head Start staff, per their usual routine. Referrals will be made

according to criteria specified in the grant application.

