#### Outcome measures (\*denotes primary outcome measure)

| Outcomes                                                      | Operationalization of variable                                    | Timing of data collection after baseline |
|---------------------------------------------------------------|-------------------------------------------------------------------|------------------------------------------|
| i. Problem Solving Skills*                                    | Calculated problem solving index from SPSI-R                      | 6, 12 months                             |
| ii. Incident rate of moderate to severe symptomatic episodes* | QIDS score $\geq 11$ , corresponding to 'moderate' symptomatology | 2, 4, 6, 8, 10, 12 months                |
| iii. Depressive symptoms over time*                           | Mean QIDS scores over time                                        | 2, 4, 6, 8, 10, 12 months                |
| iv. Social and parenting functioning                          | Mean SAS-SR and PSI scores                                        | 6, 12 months                             |
| v. Receipt of mental health services                          | Standardized questionnaire                                        | monthly recall                           |
| vi. Head Start attendance                                     | Head Start records, analyzed as monthly absence rates             | monthly reports                          |

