### Sample Size Justification

Based on empiric longitudinal data that we have collected among a cohort of Head Start mothers, we describe the size of detectable interventional effects with adequate statistical power for each primary outcome. All estimates assume 80% power and a two-sided alpha of 0.05.

- i. Problem solving skills. The mean problem solving (SPSI-R) score among mothers in our observational study is 12.2, (SD 2.5); women with  $\geq$  moderate depression symptoms have a mean score of 14.7 (SD 2.2) and those with  $\leq$  mild symptoms have a mean score of 9.8 (SD 2.8;  $p > 0.0001$ ). Using a two-sample t-test, a sample size of 100 per group will be able to detect a very granular one-point difference in mean SPSI-R scores between study groups (a standardized effect size of 0.4).

- ii. Incident rate of moderate to severe symptomatic episodes. Using poisson regression analysis, with 100 subjects in each study group and a poisson rate of 1.2 spikes per 5 follow-up assessments in the control group (according to our current data), we can detect a reduction in the rate of spikes to 0.8 in the treatment group – a 33% reduction in symptomatic episodes.
- iii. Depressive symptoms over time. In our longitudinal data, we have observed the following mean QIDS scores for each follow-up month and assume these values for the control group in the planned study: 8.2; 7.6; 7.5; 6.9; 7.2 (common SD, 5.9). We hypothesize that the following mean QIDS scores in the treatment group would be achievable and clinically significant: 7.2; 6.6; 5.5; 4.4; 4.2, resulting in a mean difference of 3 points in QIDS scores across study groups (note: a 3-point difference in QIDS scores, in the majority of cases, would move a subject across a clinical cutoff corresponding to mild, moderate or severe symptoms). Using a two group repeated measures design analyzed by generalized estimating equations or mixed linear models, noting within-subject correlations of 0.7 for values separated in time by one month and 0.6 for those separated for two months or more in our longitudinal analysis), we can detect the above differences in the means between groups over time with 100 subjects per study group.

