### Data Analysis

Our analysis plan conforms to CONSORT guidelines. We will record the number of families approached, screened, ineligible, and refusing participation. We will assess the success of randomization by comparing baseline characteristics between groups. We will record subject attrition and note all adverse events. To estimate intervention effect, we will conduct an intention-to-treat analysis to compare the difference between intervention and control groups for all primary and secondary outcome measures. The following primary outcomes will be analyzed accordingly:

- i. Problem solving skills. We will employ two sample t-tests to compare mean problem solving scores between groups. If significant baseline differences exist across groups, we will employ linear regression analysis to adjust for these differences.
- ii. Incident rate of moderate to severe symptomatic episodes. We will employ Poisson regression techniques to compare rates of elevations in QIDS scores to  $\geq 11$  (moderate symptomatology) over the 12 months of follow-up.
- iii. Depressive symptoms over time. We will use generalized estimating equations or mixed linear models to examine group-by-time effects on mean QIDS scores over the 12 months of follow-up.

Using generalized mixed models for each of these outcomes (to which the above analytic methods can be extended), we will also investigate the impact of Head Start enrollment site as a clustering effect. As an exploratory analysis, we will also examine additional clustering of PSE clients by educator.

This analysis plan, taken from our grant application, will be reproduced in our IRB application.

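### The primary SPSI-R comparison adjusts for baseline only after a significance test, so the baseline score that every mother provides will usually go unused

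*Protocol*

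**What the plan says.** The outcome table in the protocol's Outcomes section stars problem solving as a primary outcome, operationalized as "Calculated problem solving index from SPSI-R" at 6 and 12 months. Data Analysis, item i, fixes the method: "We will employ two sample t-tests to compare mean problem solving scores between groups". The next sentence sets the only route to adjustment: "If significant baseline differences exist across groups, we will employ linear regression analysis to adjust for these differences". Earlier in the same section the plan states: "We will assess the success of randomization by comparing baseline characteristics between groups". Neither the variables to be tested nor a significance threshold is named.

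The Procedure section introduces the pre-randomization survey with "we will collect the following data from all mothers enrolled in the study", and item h of that survey is the Social Problem Solving Inventory. The Design section stratifies randomization by Head Start site and by presence or absence of depression history. Neither factor enters the t-test. The paragraph that closes Data Analysis extends the methods to mixed models in order to examine clustering by site and, as exploration, by educator. It neither adds baseline SPSI-R nor withdraws the conditional rule.

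**The concern.** In a properly randomized trial, any baseline difference between arms is due to chance. A significance test on it says nothing about whether the variable predicts the outcome, and prediction is the reason to adjust. The baseline value of the outcome measure is usually among the strongest predictors available. Under item i it is used only when the arms happen to differ markedly on it, and left out otherwise.

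Three things follow:
- Precision is given up on a primary outcome.
- A sizeable but non-significant imbalance in baseline SPSI-R, the situation in which adjustment matters most to the credibility of the result, goes uncorrected.
- The primary model is not known until the baseline data have been inspected, and it depends on which variables someone chooses to test.

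The protocol itself states this rule, so it is not a detail left to a later analysis plan.

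**Working it through.** **Inputs.** From Sample Size Justification: a one-point difference, SD 2.5, 100 analysable mothers per arm, and "All estimates assume 80% power and a two-sided alpha of 0.05". From Design: 1:1 allocation. The correlation r between baseline and follow-up SPSI-R is not given, so r = 0.3 to 0.7 is an assumption. The only within-subject correlations in the protocol are 0.7 and 0.6, and they are for QIDS. The calculation treats a single follow-up score.

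**Step 1: the plan's own figure.**
- n per arm = 2 × (1.96 + 0.84)² × 2.5² / 1² ≈ 98.1, rounded up to 99.
- Power at 100 per arm = Φ(1 / (2.5 × √(2/100)) − 1.96) = Φ(2.83 − 1.96) = 80.7%. With the noncentral t distribution it is 80.4%.

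The stated 100 per group is therefore right for an unadjusted t-test on these inputs.

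**Step 2: always adjusting for baseline SPSI-R.** The residual SD becomes 2.5 × √(1 − r²). Example at r = 0.5: 2.5 × √0.75 = 2.165, and power = Φ(1 / (2.165 × √0.02) − 1.96) = Φ(3.27 − 1.96) = 90.4%.

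| Assumed r | Power, 100 per arm | n per arm for 80% | Detectable difference (points) |
|---|---|---|---|
| unadjusted | 80.7% | 99 | 0.99 |
| 0.3 | 84.3% | 90 | 0.95 |
| 0.4 | 87.0% | 83 | 0.91 |
| 0.5 | 90.4% | 74 | 0.86 |
| 0.6 | 94.2% | 63 | 0.79 |
| 0.7 | 97.7% | 51 | 0.71 |

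**Step 3: the rule as written.** This was simulated with 40,000 trials per setting, 100 per arm, normal scores, and baseline SPSI-R as the only variable tested, at 0.05. The t-test is used if that test is not significant and ANCOVA if it is. The pre-test was significant in about 5% of trials, as it must be.

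| Assumed r | Power, two-step rule | Power, ANCOVA always | Overall type I error, two-step rule |
|---|---|---|---|
| 0.3 | 80.6% | 83.5% | 4.8% |
| 0.5 | 81.7% | 90.2% | 4.2% |
| 0.6 | 81.9% | 93.8% | 3.8% |
| 0.7 | 82.5% | 97.5% | 3.6% |

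The gap runs from 83.5 − 80.6 = 2.9 points to 97.5 − 82.5 = 15.0 points. Overall error falls below 5% because the unadjusted test's false positives cluster in trials with large imbalance, and those are the trials the rule moves to ANCOVA.

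**Step 4: imbalance that just misses significance.** Among null trials whose baseline t-statistic lies between 1.5 and about 1.97 in absolute value, the unadjusted test rejects in 7.2%, 9.4%, 11.6% and 14.2% for r = 0.3, 0.5, 0.6 and 0.7. ANCOVA rejects in 4.7% to 5.7%. As a hand check, given a baseline t of 1.7, the follow-up t is roughly normal with mean 1.7r and SD √(1 − r²). At r = 0.6 the mean is 1.02 and the SD 0.8, so the chance of exceeding 1.96 is 1 − Φ(0.94/0.8) = 1 − Φ(1.175) ≈ 12%, in line with the simulation.

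**Step 5: how open the model is.** If k independent baseline variables were each tested at 0.05, the chance that at least one triggers regression is 1 − 0.95^k, which is 40% for k = 10 and 54% for k = 15. This is illustrative, because the protocol does not say how many would be tested and the survey scales are unlikely to be independent.

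**The case against.** An unadjusted t-test in a 1:1 randomized trial gives an unbiased estimate. It matches the method used to size the trial, and it reaches the planned power on the stated inputs. Randomization is already stratified by site and depression history. The error rates in Step 4 are conditional: any unadjusted test has them, and they average out over randomizations. The size of the gain rests on an assumed correlation. All of this stands, and it limits how serious the point is. It does not justify the conditional rule, which recovers almost none of the available precision and leaves the covariates open.

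Three stronger readings are tempting and are not supported:
- A reader might infer that the pre-test makes the p-value invalid by inflating false positives. With SPSI-R alone tested, overall error is at or slightly below nominal. Selection among many covariates could matter more, but the protocol does not say that the choice would be made with outcomes in view.
- A reader might infer that real power is well below 80%, because the symptom-subgroup means and SDs in Sample Size Justification can be combined into an overall SD above 2.5. That is a separate question about the SD input. It concerns an observational cohort, whereas the trial excludes mothers in a current major depressive episode, and it is not a consequence of the adjustment rule.
- A reader might extend the point to the Poisson analysis of QIDS episodes. There the protocol is silent on covariates, and a statistical analysis plan may settle them. No faulty rule is fixed there.

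**Conclusion.** The point holds for item i alone. The protocol fixes an unadjusted default and a significance-triggered adjustment for a primary outcome whose baseline value it already collects. Baseline SPSI-R goes unused by default, though not in every case: at a 0.05 threshold it would enter in about one trial in twenty. The cost is a loss of about 3 to 15 percentage points of power for r = 0.3 to 0.7 at SD 2.5, no correction for near-significant imbalance, and a primary model that is settled only after baseline data are seen. The direction of the power loss does not depend on the exact correlation, but its size does. The effect estimate is not biased, the sample size is not wrong for the test it assumes, and overall type I error is not shown to be inflated. This should be fixed, but it does not threaten the trial's validity.

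**What to change.** Replace item i with one pre-specified linear model for SPSI-R: either ANCOVA, or a mixed model of the 6- and 12-month scores. The model always includes baseline SPSI-R and the two stratification factors, site and depression history, whatever the baseline comparison shows. Delete the sentence that makes adjustment conditional on significant differences. The baseline table can stay as description but should not drive the choice of model. The unadjusted t-test can be kept as a supporting analysis.

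The cost is wording in the protocol and in any analysis plan. No additional measure, visit or participant is needed, and the sample size can stand, since adjustment for a predictive baseline score can be expected to add power to the unadjusted calculation.

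### The primary SPSI-R comparison uses the baseline SPSI-R score only if a baseline significance test is positive, which wastes precision and leaves the primary model unfixed until the arms are compared

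*Protocol*

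**What the plan says.** Data Analysis, item i, sets the primary analysis of problem solving: "We will employ two sample t-tests to compare mean problem solving scores between groups". The next sentence makes any adjustment conditional: "If significant baseline differences exist across groups, we will employ linear regression analysis to adjust for these differences". It does not say which baseline variables are tested, at what level, or which of them would enter the regression. The opening paragraph of the same section announces the comparison that would feed this rule: "We will assess the success of randomization by comparing baseline characteristics between groups".

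The Sample Size Justification uses the same unadjusted test: "Using a two-sample t-test, a sample size of 100 per group will be able to detect a very granular one-point difference in mean SPSI-R scores", described as "a standardized effect size of 0.4".

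Under Procedure, the Baseline Survey is taken from all enrolled mothers before randomization, and its item h is the Social Problem Solving Inventory. The Outcomes table lists the SPSI-R index as a primary outcome at 6 and 12 months. Under Design, randomization is carried out separately within each Head Start site and within strata of depression history. The sentence on generalized mixed models that closes the Data Analysis section concerns clustering by site and by educator and adds no baseline covariate. No other section commits to adjusting SPSI-R for its baseline value.

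**The concern.** After randomization, a difference between the arms at baseline is due to chance. Its p-value does not show whether the variable predicts the outcome, and prediction is what makes a covariate worth including. Under the stated rule a baseline score that predicts follow-up is left out of most trials, while a variable of no prognostic value could enter because it happened to differ.

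Three things are at stake. First, precision on a primary outcome is given up although the data are already in hand. Second, an imbalance in baseline SPSI-R just short of significance passes uncorrected into the estimate. Third, whether the primary result comes from a t-test or a regression, and on which covariates, is settled only after the arms have been compared.

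**Working it through.** **Inputs from the protocol (Sample Size Justification).** Difference 1 point, SD 2.5, n = 100 per group, and "All estimates assume 80% power and a two-sided alpha of 0.05".

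**Inputs assumed.** The correlation r between baseline and follow-up SPSI-R is not given, so a range of 0.3 to 0.7 is used. The only within-subject correlations in the protocol (0.6 to 0.7) are for the QIDS. The level of the baseline test is not given either; 5% is assumed.

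**1. The plan's own figure.** n per group = 2 × (1.960 + 0.842)² × 2.5² / 1² = 98.1, rounded up to 99. At n = 100 the standard error is 2.5 × √(2/100) = 0.354, so 1/0.354 = 2.83 and power = Φ(2.83 − 1.96) = 80.7% (80.4% by the non-central t). The stated 100 per group is reproduced.

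**2. Always adjusting for baseline SPSI-R.** The residual SD is 2.5 × √(1 − r²), and power = Φ(2.83/√(1 − r²) − 1.96). For example, at r = 0.6 the residual SD is 2.0, 2.83/0.8 = 3.54, and Φ(1.58) = 94.2%.

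**3. The stated rule, with baseline SPSI-R as the only trigger.** Simulation with 100 per arm and 100,000 trials per setting: regression on baseline if the baseline test is significant at 5%, otherwise the t-test. The trigger fires in about 5% of trials, so about 95% use the unadjusted test.

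| r | Power, always adjusted (formula) | n per group for 80% power, always adjusted | Power, stated rule (simulated) | Overall type I error, stated rule |
|---|---|---|---|---|
| 0.3 | 84.3% | 90 | 80.7% | 4.8% |
| 0.4 | 87.0% | 83 | not simulated | not simulated |
| 0.5 | 90.4% | 74 | 81.5% | 4.3% |
| 0.6 | 94.2% | 63 | 82.0% | 4.0% |
| 0.7 | 97.7% | 51 | 82.2% | 3.6% |

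In the same simulation, always adjusting gave 83.7%, 90.0%, 94.1% and 97.6% at r = 0.3, 0.5, 0.6 and 0.7. The rule therefore gives up about 3 points at r = 0.3 and about 15 points at r = 0.7.

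**4. Imbalance just short of significance.** The baseline t statistic lies between 1.5 and 1.97 in absolute value in about 8% of trials (0.134 − 0.050 = 0.084). In those trials the rule leaves the imbalance uncorrected. Conditional type I error is then 6.5%, 10.2%, 11.9% and 13.8% at r = 0.3, 0.5, 0.6 and 0.7, against about 5% with adjustment.

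**5. If any baseline variable can trigger adjustment.** The Baseline Survey has 17 distinct instruments apart from demographics, counting the two instruments in item d and the two in item i separately, and behavioral activation once. If they were independent, the chance that at least one differs at 5% is 1 − 0.95¹⁷ = 58%. With a common correlation of 0.3 it is 49%, and with 0.5 it is 39%. This is a different reading of the sentence from step 3, and the power figures there do not apply to it.

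**The case against.** The strongest defence is that the t-test delivers what the plan promises. It has 80% power on the stated inputs, and the two-step rule does not inflate the overall type I error. Both statements are right. A reader might infer from the conditional rule that the trial is underpowered or that its primary test is invalid. The documents do not support either inference: the sample size was set for the unadjusted test, and with baseline SPSI-R as the trigger the overall error is at or below the nominal 5%.

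The gain also rests on a correlation that the protocol does not report. The QIDS values were observed for a different scale and cannot simply be carried over to SPSI-R at 6 and 12 months. At r = 0.3 the gain is only 3 to 4 points. This limits the size of the point but not its direction, since within the assumed range adjusting always does better than the rule.

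The wording of the trigger is open. It stands under the problem-solving item, so it may mean baseline problem-solving scores alone. In that case the covariate is known, the trigger rate is about 5%, and the 58% figure falls away. If it means any baseline variable, 58% is an upper figure: the measures are correlated, and mothers in a current major depressive episode on the M.I.N.I. are excluded, so that instrument has little room to differ. A reader might put the low trigger rate of one reading beside the high trigger rate of the other, but each belongs to its own reading.

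Finally, the conditional error rates describe about one trial in twelve and are not the error rate of the design. A larger figure could be had by conditioning on one imbalance just below the threshold, but such an imbalance is rare.

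A separate statistical analysis plan may exist. That does not answer the point, because the protocol itself states the conditional rule for a primary outcome.

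**Conclusion.** The point holds as a matter of efficiency and prespecification, and it should be fixed. The protocol leaves a baseline measure that it collects from everyone out of the primary model unless an uninformative test is positive. For an assumed r of 0.3 to 0.7 this forgoes roughly 3 to 15 points of power. It also leaves near-significant imbalances uncorrected and lets the observed arms decide the primary model. The trial remains valid and adequately powered on its own inputs. The power figures assume SD 2.5, a 1-point difference, 100 analyzable mothers per group and normally distributed scores. The figures for the rule further assume a 5% baseline test on SPSI-R alone.

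**What to change.** Replace item i with a model that is the same whatever balance is observed: linear regression (ANCOVA) of SPSI-R at 6 and at 12 months on arm and baseline SPSI-R, or a mixed model over both visits with the same terms. Include the randomization strata, site and depression history, in either model. Say which visit, or which combination of the two, carries the primary comparison, since the Outcomes table lists both.

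Delete the sentence that makes adjustment depend on significant baseline differences. Describe baseline characteristics by arm without significance tests. Keep the unadjusted t-test as a sensitivity analysis.

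The cost is a few sentences of analysis text. No further mothers, visits or instruments are needed, and the sample size can stay as planned.

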8. Outcome assessments: Each subject will have a 12-month follow up period, during which blinded research assistants will assess outcome measures. Follow-up data collection will begin 2 months after baseline because a full, 6-session course of PSE typically lasts 6-8 weeks. To limit attrition, we will employ a combination of monetary incentives and postcard reminders. Through these strategies, approved by the BUMC IRB in our pilot work, we have been able to maintain follow up rates > 85% across all relevant ongoing studies (there is a separate section on participant compensation in the protocol manual).

Baseline, 6-month, and 12-month assessments will take place in person with a staff RA. We will administer the QIDS and mental health service use questions on a bimonthly basis throughout the study period, and this will be done by telephone by a staff RA.

The 6-month interview will comprise the following valid and reliable scales:

- a. Perceived Stress Scale
- b. M.I.N.I. Depression Module
- c. QIDS
- d. Mental Health Service Use questions (adapted from Collaborative Psychiatric Epidemiology Surveys)
- e. Social functioning (Social Adjustment Scale-Self Report)
- f. Parenting Stress Index
- g. Problem Solving Questions (Social Problem Solving Inventory)
- h. Coping Questions (Brief COPE)
- i. Pearlin Mastery Scale
- j. Behavioral Activation for Depression Scale
- k. Rosenberg Self-Esteem Scale

The 12-month interview will comprise the following valid and reliable scales:

- a. Perceived Stress Scale
- b. M.I.N.I. Depression Module
- c. QIDS
- d. Mental Health Service Use questions (adapted from Collaborative Psychiatric Epidemiology Surveys)
- e. Social functioning (Social Adjustment Scale-Self Report)
- f. Problem Solving Questions (Social Problem Solving Inventory)
- g. Coping Questions (Brief COPE)
- h. Pearlin Mastery Scale
- i. Behavioral Activation for Depression Scale
- j. Rosenberg Self-Esteem Scale
- k. Recent Life Changes Questionnaire

- I. Mood, anxiety and alcohol and other substance use, modules of the SCID

RA's will be trained not to leave telephone messages, and to introduce themselves as from "BMC" so as to ensure confidentiality.

9. At 6-months post randomization, parents and Head Start teachers will be asked to fill out the Social Skills Rating System (SSRS) with reference to all 3-5 year-old Head Start children of enrolled parents.
10. We will assess rate of absenteeism from Head Start for children of mothers who are in our study.

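### The primary QIDS analysis tests group-by-time and names no baseline adjustment; a baseline-adjusted average arm difference would guard against an early, sustained benefit at no cost

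*Protocol*

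**What the plan says.** Data Analysis, item iii, plans generalized estimating equations or mixed linear models to "examine group-by-time effects on mean QIDS scores over the 12 months of follow-up". Baseline adjustment appears only in item i (problem solving), and there only if the arms differ significantly at baseline.

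The Outcome measures table lists the outcome as "Mean QIDS scores over time", collected at months 2, 4, 6, 8, 10 and 12 after baseline. Procedure, item 8, explains the start: "Follow-up data collection will begin 2 months after baseline because a full, 6-session course of PSE typically lasts 6-8 weeks". Procedure, item 5, puts the QIDS in the baseline survey, which is completed before randomization.

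Sample Size Justification, item iii, assumes treatment means of "7.2; 6.6; 5.5; 4.4; 4.2, resulting in a mean difference of 3 points in QIDS scores across study groups", quotes "within-subject correlations of 0.7 for values separated in time by one month and 0.6 for those separated for two months or more", and concludes that "we can detect the above differences in the means between groups over time with 100 subjects per study group". It uses follow-up means only. Aim 2 in Background/Rationale/Purpose includes reducing depressive symptoms over time. The opening of Data Analysis commits to an intention-to-treat comparison of the two groups on every primary outcome.

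**The concern.** A group-by-time term measures change in the arm difference, not the difference itself. On visits that start at about the end of the course, it asks whether the arms separate further from month 2 onward. A mother whose symptoms fall during the course and stay lower is a success for aim 2, yet that pattern contributes nothing to the interaction.

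At stake is whether one of three primary outcomes can register a plausible form of benefit. The baseline QIDS score, which would sharpen the direct comparison of arms, is already collected but has no stated role in this model.

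**Working it through.** **Inputs** (Sample Size Justification): SD 5.9; 100 analysable mothers per group; "All estimates assume 80% power and a two-sided alpha of 0.05". Planned visits are two months apart, so the correlation between visits is taken as 0.6 throughout.

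Control minus treatment means at the five listed assessments:

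| Assessment | 1 | 2 | 3 | 4 | 5 |
|---|---|---|---|---|---|
| Control | 8.2 | 7.6 | 7.5 | 6.9 | 7.2 |
| Treatment | 7.2 | 6.6 | 5.5 | 4.4 | 4.2 |
| Difference | 1.0 | 1.0 | 2.0 | 2.5 | 3.0 |

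The average is 9.5/5 = 1.9. The 3-point figure in the text is reached only at the last assessment, so 1.9 is used below.

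**Reproducing the plan's figure.**
- Average difference: the variance factor is (1 + 4 × 0.6)/5 = 0.68. SE = 5.9 × √(0.68 × 2/100) = 0.688; 1.9/0.688 = 2.76; power 79%.
- Group-by-time, 4 df: the squared deviations of the differences from 1.9 sum to 3.20. Noncentrality = 100 × 3.20/(2 × 5.9² × 0.4) = 11.49; power 78%.

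Both are close to the stated 80%.

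**Follow-up slope, growing pattern.** With weights -2, -1, 0, 1, 2 the contrast is 5.5. SE = √(5.9² × 0.4 × 10 × 2/100) = 1.669; 5.5/1.669 = 3.30; power 91%.

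**Constant 1.9-point benefit, follow-up visits only.** Every deviation from the mean difference is zero, so noncentrality is 0 and power is 5% at any sample size. The same holds for a constant 3-point benefit.

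**Constant 1.9-point benefit, baseline as a time-0 response** (SD 5.9, correlation 0.6 with follow-up, no difference at baseline).
- Categorical time: the differences 0, 1.9, 1.9, 1.9, 1.9, 1.9 have squared deviations summing to 3.008. Noncentrality = 100 × 3.008/(2 × 5.9² × 0.4) = 10.80 on 5 df; power 72%.
- Linear time: contrast 4.75 with variance 5.9² × 0.4 × 17.5 × 2/100 = 4.873. Noncentrality = 4.75²/4.873 = 4.63; power 58%.

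**Baseline-adjusted average.** Adjustment subtracts r² from the factor 0.68, where r is the correlation of baseline with each follow-up score. The protocol does not give r separately, so a range is shown.

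| r (assumed) | Factor | SE | 1.9/SE | Power |
|---|---|---|---|---|
| 0.3 | 0.59 | 0.641 | 2.96 | 84% |
| 0.4 | 0.52 | 0.602 | 3.16 | 88% |
| 0.5 | 0.43 | 0.547 | 3.47 | 93% |
| 0.6 | 0.32 | 0.472 | 4.03 | 98% |

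**Summary of power, 100 per arm**

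| Analysis | Constant 1.9 | Protocol's growing pattern |
|---|---|---|
| Group-by-time, follow-up only, 4 df | 5% | 78% |
| Slope, follow-up only | 5% | 91% |
| Group-by-time, baseline at time 0, categorical | 72% | 97% |
| Group-by-time, baseline at time 0, linear | 58% | over 99% |
| Unadjusted average | 79% | 79% |
| Baseline-adjusted average, r = 0.3 to 0.6 | 84% to 98% | 84% to 98% |

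Under the growing pattern the adjusted average matches the follow-up slope when 1.9/SE = 3.30. That means SE = 0.576, factor 0.477, and r = √(0.68 - 0.477) = 0.45.

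**Sensitivity.** With correlation 0.7 between adjacent visits and 0.6 otherwise, the growing pattern gives 69% (4 df), 85% (slope) and 77% (unadjusted average). The adjusted average has 82%, 87%, 92% and 97% for r = 0.3, 0.4, 0.5 and 0.6. Using all six planned visits instead of five changes little: for a constant 1.9 points the unadjusted average has 80%, and the adjusted average at r = 0.6 has 98%.

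**The case against.** The protocol never says that baseline QIDS is left out of the model. The table column that omits baseline is headed as timing after baseline, so it could not list it. Treating baseline as time 0 is a common reading, and then the test is weaker for a constant benefit but not blind to it. This stands: a reader might infer that an early benefit would certainly be missed, and the documents support that only under the follow-up-only reading.

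The protocol also hypothesises a growing difference, and monthly booster calls continue after the course, so further separation after month 2 is plausible. This stands too. Under that pattern a slope test suits the hypothesis, and the unadjusted average (79%) is weaker than the follow-up slope (91%). Any advantage of the proposed contrast then comes wholly from baseline adjustment. If baseline is already a time-0 response with correlation 0.6, group-by-time does about as well or better (97% to over 99%).

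The 98% figure rests on carrying the 0.6 from an observational cohort over to baseline in this trial. Entry here is restricted to mothers who are at risk but not in a major depressive episode, which could lower the correlation.

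Two further inferences are not supported. A reader might say that the test conflicts with the sample-size text. But that text speaks of differences between groups over time, and the 4-df interaction gives 78%, so no conflict is shown. A reader might also say that generalized estimating equations must be dropped. That choice, like the covariance structure, is detail that can be left to a statistical analysis plan.

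Finally, the second primary outcome, the rate of QIDS scores of 11 or more, could register a sustained benefit. Aim 2 is therefore not left wholly unanswered; the weakness concerns the third primary outcome.

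**Conclusion.** The point holds in a conditional form and is worth acting on. The protocol itself fixes group-by-time as the tested effect, so this is not merely detail awaiting an analysis plan.

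- For a benefit present by month 2 and held constant, the named test has 5% power if only follow-up visits are modelled. It has 72% or 58% for a 1.9-point benefit if baseline is a time-0 response. The baseline-adjusted average has 84% to 98%. At the common assumption of 0.6 for the baseline correlation, the comparison with the time-0 reading is 72% or 58% against 98%.
- For the protocol's growing pattern, the adjusted average beats the follow-up 4-df test (78%) across the assumed range. It beats the follow-up slope (91%) only if the baseline correlation is about 0.45 to 0.5 or more, and it does not improve on a time-0 linear analysis.

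The case for change is therefore protection against one plausible effect shape and a direct estimate of the arm difference, not a uniform gain in power. It rests on SD 5.9, correlation 0.6 between visits, 100 analysable mothers per arm, a 1.9-point average benefit and the assumed range for the baseline correlation.

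**What to change.** In Data Analysis, item iii, state that the model for QIDS at months 2 to 12 includes the pre-randomization QIDS score as a covariate, together with the randomization strata (Head Start site and depression history). Make the average arm difference over months 2-12 the primary contrast. Keep the group-by-time effect as a secondary description of how the difference develops.

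This changes wording only: no new data, visits or mothers are needed. The one downside is that if the effect appears only late and the baseline correlation is low, the average contrast is somewhat less powerful than a slope test (for example 84% against 91% at a baseline correlation of 0.3).
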